# Therapeutic drug monitoring guided dosing versus standard dosing of alectinib in advanced ALK positive non-small cell lung cancer patients: Study protocol for an international, multicenter phase IV randomized controlled trial (ADAPT ALEC)

**DOI:** 10.3389/fonc.2023.1136221

**Published:** 2023-03-09

**Keywords:** non-small cell lung cancer, anaplastic lymphoma kinase, protein kinase inhibitors, therapeutic drug monitoring, randomized controlled trial, pharmacokinetics, personalized dosing, cost-effectiveness

## Abstract

**Background:**

Alectinib is first-line therapy in patients with stage IV non-small cell lung carcinoma (NSCLC) and an anaplastic lymphoma kinase (ALK) fusion. A shorter median progression-free survival (mPFS) was observed when alectinib minimum plasma concentrations during steady state (C_min,SS_) were below 435 ng/mL. This may suggest that patients should have an alectinib C_min,SS_ ≥ 435 ng/mL for a more favorable outcome. This potential target could be attained by using therapeutic drug monitoring (TDM), i.e. adjusting the dose based on measured plasma trough concentrations. Hypothetically, this will increase mPFS, but this has not yet been evaluated in a randomized controlled trial (RCT). Therefore, the ADAPT ALEC trial is designed, with the primary objective to prolong mPFS in NSCLC patients treated with alectinib by using TDM.

**Methods:**

ADAPT ALEC is a multicenter, phase IV RCT, in which patients aged ≥ 18 years with advanced ALK positive (+) NSCLC eligible for alectinib in daily care are enrolled. Participants will be randomized (1:1 ratio) into intervention arm A (TDM) or B (control), stratified by brain metastases and prior ALK treatments. Starting dose in both arms is the approved flat fixed dose of alectinib 600 mg taken twice daily with food. In case of alectinib C_min,SS_ < 435 ng/mL, arm A will receive increased doses of alectinib till C_min,SS _≥ 435 ng/mL when considered tolerable. The primary outcome is mPFS, where progressive disease is defined according to RECIST v1.1 or all-cause death and assessed by CT-scans and MRI brain. Secondary endpoints are feasibility and tolerability of TDM, patient and physician adherence, overall response rate, median overall survival, intracranial PFS, quality of life, toxicity, alectinib-M4 concentrations and cost-effectiveness of TDM. Exploratory endpoints are circulating tumor DNA and body composition.

**Discussion:**

The ADAPT ALEC will show whether treatment outcomes of patients with advanced ALK+ NSCLC improve when using TDM-guided dosing of alectinib instead of fixed dosing. The results will provide high quality evidence for deciding whether TDM should be implemented as standard of care and this will have important consequences for the prescribing of alectinib.

**Clinical trial registration:**

ClinicalTrials.gov, identifier NCT05525338.

## Introduction

1

The identification of targetable oncogenic driver mutations and the introduction of tyrosine kinase inhibitors (TKIs) as targeted therapy in non-small cell lung cancer (NSCLC) improved the survival of NSCLC patients considerably (1–4). In the Netherlands, in 1.3% of the patients with advanced NSCLC an anaplastic lymphoma kinase (ALK) fusion is detected, which make these patients eligible for targeted therapy with an ALK TKI (5). Alectinib was registered in 2015 as second-line therapy in ALK positive (+) patients, after first-generation ALK TKI crizotinib (6). This changed after publication of the randomized phase III J-ALEX and ALEX trials, where alectinib showed improved median progression-free survival (mPFS) compared to crizotinib (7, 8). Ever since, alectinib is standard of care in first- and second-line setting in ALK+ NSCLC treatment (9, 10). In updated overall survival (OS) data of the ALEX trial, the median OS of alectinib was not reached, whereas the median OS of crizotinib was 57.4 months (stratified hazard ratio (HR) 0.67, P = 0.0367), median follow-up durations were 48.2 months and 23.3 months respectively (11). Therefore, alectinib showed meaningful improvement of the OS compared to crizotinib.

The approved standard dose of alectinib in Europe is a fixed dose of 600 mg twice daily (BID) (12). A retrospective exposure-response analysis of alectinib showed that mPFS was significantly longer in patients with an exposure above the minimum plasma concentration during steady state (C_min,SS_) of 435 ng/mL compared to patients with trough levels < 435 ng/mL (13). This suggests that patients with alectinib C_min,SS_ ≥ 435 ng/mL had a more favorable outcome. The median alectinib C_min,SS_ per patient was 517 ng/mL (range: 141-1944 ng/mL), with an interindividual variability of 57% (13). Available data support pharmacokinetic (PK) guided dose increases in patients with low exposure, with C_min,SS_ ≥ 435 ng/mL as a proposed target. This could be attained by using therapeutic drug monitoring (TDM), i.e. adjusting the dose based on measured plasma concentrations in the individual patient.

However, in another exposure-response analysis, no association was found between OS and trough levels of both alectinib and the active metabolite M4 (14). Therefore, the evidence for TDM-guided dosing of alectinib is conflicting, as results of two performed exposure-response analyses were not consistent with each other (13, 14). This stressed the high demand for prospective randomized controlled trials (RCTs) to ensure the level of evidence of TDM of TKIs including alectinib. Recently, a prospective multicenter study by the Dutch Pharmacology Oncology Group showed TDM-guided dosing of various oral targeted anti-cancer agents to be feasible in clinical practice, which resulted in a reduced proportion of patients with a C_min,SS_ below the proposed target. For alectinib only 14 evaluable patients were included, of which two received a successful dose intervention (15). Based on this data, it cannot yet be said whether TDM has a potential clinical benefit for alectinib. While the exposure-response analysis suggests a potential clinical benefit of TDM-guided dosing of alectinib, there is not enough support yet for its implementation in clinical practice. For this reason, there is a great demand to study the clinical benefit of TDM in an RCT.

In this paper, we present the outline of the ADAPT ALEC trial: a prospective, multicenter, phase IV, RCT to study the clinical benefit of TDM in patients with advanced ALK+ NSCLC. The obtained study results will address the question whether personalized dosing results in a significant difference in the treatment outcomes of individual patients with ALK+ NSCLC.

## Methods and analysis

2

### Aim and objectives

2.1

The aim of this RCT is to investigate the effect of TDM-guided dosing of alectinib on treatment outcomes of patients with ALK+ NSCLC. We hypothesize that using TDM to increase the dose of alectinib in patients with C_min,SS_ < 435 ng/mL if tolerable, will raise the mPFS. The primary objective will be to demonstrate, among patients who had a C_min,SS_ < 435 ng/mL at any time point during treatment, a prolonged mPFS in the TDM-guided dosing arm compared to the fixed dosing arm. Feasibility and tolerability of TDM, patient and physician adherence, overall response rate (ORR), median overall survival (mOS), intracranial PFS, quality of life (QoL), toxicity, alectinib-M4 concentrations and cost-effectiveness of TDM will be evaluated as secondary objectives. In addition, exploratory data will be collected on circulating tumor DNA (ctDNA) and its association with response and types of resistance to therapy. Data regarding the influence of alectinib on body composition will also be collected as exploratory objective, as weight gain is a known but not well understood side-effect.

### Study design

2.2

The ADAPT ALEC trial is an international, multicenter, phase IV, RCT comparing TDM-guided dosing to standard dosing of alectinib. Initially the trial will be open at seven study sites in the Netherlands, after which international sites will follow. The study design is displayed in **Figure 1**. Patients will be centrally randomized according to the minimization method in a 1:1 ratio, stratified by prior treatment with other ALK inhibitors and presence of brain metastases, using the online randomization tool ALEA v.18.3 (FormsVision BV, Abcoude, The Netherlands). The trial will compare, in the subgroup of patients with alectinib plasma concentration C_min,SS_ < 435 ng/mL at any time point, those receiving dose-adjusted alectinib based on TDM (arm A) with those receiving standard treatment with fixed dose alectinib (arm B).

**Figure 1 f1:**
[figure not shown]
Schematic overview of study design. ALK, Anaplastic lymphoma kinase; BID, twice daily; C_min,SS_, minimum plasma concentration during steady state; ctDNA, circulating tumor DNA; mPFS, median progression free survival; mOS, median overall survival; ORR, overall response rate; R, Randomization; TDM, Therapeutic Drug Monitoring.

Patients who start alectinib treatment at the approved European standard dose of 600 mg BID will be screened and if eligible, randomized into arm A or B. First PK samples will be collected at 4 weeks after start of treatment. Subsequently, plasma samples will be drawn to evaluate the plasma trough concentration every 8 weeks in the first year of treatment, then every 12 weeks thereafter. Blood collection and analysis will be combined with regular safety lab measurements during standard routine visits, therefore causing limited additional burden for the patients. The flowchart consisting of the schedule of assessments can be found in **Supplemental Table 1**.

#### Intervention and control group

2.2.1

For patients in arm A (TDM group) plasma trough concentrations of alectinib will be analyzed directly from the PK samples. Results will be available within 1-2 weeks. In case of C_min,SS_ below the threshold of 435 ng/mL (in arm A) and no or limited toxicity, the patient receives a dose increase with 150 mg BID to a maximum of 900 mg BID. The dose levels are shown in **Table 1**. Four weeks after a dose increase, an extra PK sample is drawn to check whether the intervention was successful, i.e. when TDM target is reached with acceptable tolerability. When patients have adequate exposure (C_min,SS_ ≥ 435 ng/mL), the dose will be continued given no or acceptable toxicity. For patients in arm B, PK samples will be drawn conform the same schedule as patients in arm A. However, these samples will remain blinded to the patients and the treating physician until the end of the study. In case of unmanageable toxicity in both arms (i.e. unbearable or persistent grade 2 toxicity, or grade 3/4 toxicity according to Common Terminology Criteria for Adverse Events (CTCAE) v5.0), the alectinib dose can be reduced by one dose level (150 mg BID) in accordance with standard care unto a minimum of 300 mg BID. Temporary dose interruptions are allowed. If the side effects subside or are no longer present, it is allowed to increase the dose again. To estimate the C_min,SS_ of alectinib, the time of blood draw will be recorded and all patients will keep a paper diary to collect date and time of last intake of alectinib. Alectinib C_min,SS_ will be calculated with the following formula:

**Table 1 T1:** dose levels of alectinib.

Dose level	Alectinib Dose
-2	300 mg BID
-1	450 mg BID
0	600 mg BID
+1	750 mg BID
+2	900 mg BID

$$C_{min,SS}=\;C_{measured}*0.5^{\frac{dosing\;interval-TAD}{t_{1/2}}}$$

Where C_min,SS_ is the estimated minimum plasma concentration, C_measured_ the measured plasma concentration, the dosing interval is the time between two subsequent administrations, TAD is time after dose and t_1/2_ is the elimination half-life of the drug (i.e. 32 hours for alectinib). PK samples should be drawn after at least 4 hours after the last intake of alectinib (after T_max_) (16). It is assumed that this algorithm should perform equivalently, and most likely even better, as imatinib validated by Wang et al, since the half-life of alectinib is longer (16).

### Study population

2.3

A total of 196 patients will be included in the study, who will all give their written informed consent prior to performing any study related procedures. Approximately 80 patients with ALK+, stage IV NSCLC are diagnosed in the Netherlands per year (5, 17). Almost all these patients will be treated in one of the seven initial participating centers, since there is consensus in the Netherlands to refer patients with rare mutations to a center of expertise, i.e. these seven centers. The inclusion rate is expected to be 65% based on our in- and exclusion criteria. After initiation in the Netherlands, the study will also be launched in other European medical centers, starting with Gustave Roussy (Villejuif, France). This will increase the patient population and speed up the inclusion process. Therefore, it is expected the study fulfilment will be reached in 4 years of inclusion.

#### Eligibility criteria

2.3.1

The study population will consist of adult patients with locally advanced or metastatic ALK+ NSCLC [stage IIIb to IV by AJCC 8^th^ (18)], starting treatment with alectinib at the standard dose of 600 mg BID in first or second line of care. The ALK fusion must be determined by an EMA-approved test, e.g. RNA sequencing. Patients can either be chemotherapy-naïve or have received one line of platinum-based chemotherapy. Local radiotherapy to reduce pain, as well as asymptomatic and clinically stable (≥ 2 weeks, without steroid treatment) brain or leptomeningeal metastases are allowed.

Main exclusion criteria are significant concomitant diseases or conditions that are potentially aggravated by the treatment, and use of treatments that could interfere with the alectinib therapy. For the complete list of detailed eligibility criteria, see **Supplemental Table 2**.

#### Sample size calculation

2.3.2

It is expected that 48% of the patients treated with alectinib in our study will be underdosed (i.e. C_min_ < 435 ng/mL at a certain timepoint) based on the dataset of Groenland et al. (13). The observed mPFS for these patients was 12.6 months (95% confidence interval (CI): 9.2 months – not yet reached), which will serve as the assumed median in the subgroup with low exposure in the fixed-dosing group (arm B). The mPFS in the patients with C_min_ ≥ 435 ng/mL had not yet been reached (95% CI: 19.8 months – not yet reached) at the time of analysis, but the HR for the group with C_min_ < 435 ng/mL versus C_min_ ≥ 435 ng/mL was estimated as 2.5 (13). We expect that TDM-guided dosing can improve PFS in 67% of patients with a low exposure, to the extent that they obtain a similar outcome as patients with C_min_ ≥ 435 ng/mL. In this group, a HR (fixed versus TDM-guided dosing) of 2.5 is assumed. In the remaining 33% of patients, TDM-guided dose increases are expected not to be feasible due to toxicity or treatment discontinuation as a consequence of progressive disease (PD), so a HR equal to one is assumed for this subgroup. Altogether, this would result in an expected HR (fixed versus TDM-guided) of 2.0. With 67 events, a power of 80% will be obtained to detect this HR of 2 using the log-rank test and assuming a two-sided significance level of 5%. This translates into an improvement in mPFS from 12.6 months without using TDM-guided dosing to 25.2 months using TDM-guided dosing. Assuming an uniform patient accrual during 48 months and 12 months follow-up after inclusion of the last patient (total study duration of 60 months), 94 patients (47 per group) with C_min _< 435 ng/mL will need to be included for the primary analysis. Since 48% of the patients in the study are expected to have C_min _< 435 ng/mL at a certain timepoint, 196 patients will need to be recruited (13). Dropouts are expected to be kept to a minimum and it does occur, it is expected to be in the first 12 weeks, when substitution is still allowed. Dropouts are therefore not taken into account.

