Another limitation is the fact that this study protocol is based on European standard dosing, while in Japan 300 mg BID is used (29). One hypothesis is that characteristics in the Japanese population (lower body weight and different metabolism) result in relatively higher levels and that they therefore have comparable exposure at a lower dose (30, 31). We, therefore, expect that dosing based on levels in Japan will also be applicable. Patients will start from a different starting dose, in order to have levels in the same therapeutic window as the non-Japanese population.

The expected HR of 2.0 might be slightly challenging, with the risk of ending up with a negative study. With a less extreme HR we would have needed more events and the feasibility of the study would be compromised. The HR of 2.0 is a compromise between a realistic but clinically relevant difference and the feasibility of the study. We therefore believe that the HR is achievable and will not compromise the study.

It is expected that patients will be willing to participate, since the additional burden for patients is minimal. Patients in arm B will not receive a dose increase in case of low exposure, which could be considered unethical as plasma (trough) concentrations are measured but not acted upon. However, arm B represents the patients treated according to current guidelines and thus receiving standard care which is acceptable. Furthermore, many patients are recruited from which only a fraction will be used in the analysis of the primary endpoint and some secondary endpoints, because in forehand it is unknown whether patients will have low or high alectinib exposure. We accept this as the additional burden for all patients is minimal and the obtained data of all patients will provide high quality insights for our secondary endpoints.

Comparing TDM-guided dosing versus standard dosing in a randomized clinical trial setting is the ultimate way to investigate the clinical relevance of practicing TDM of alectinib. The ADAPT ALEC trial has the potential to provide high quality evidence for deciding whether TDM should be implemented as standard of care in alectinib therapy.

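### The expected HR of 2.0 is an arithmetic mean of ratios and does not follow from the 67%/33% assumption, which gives about 1.83 and, with the planned patients and events, about 69% power rather than 80%

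*Protocol article*

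**What the plan says.** Section 2.3.2 (Sample size calculation) builds the effect size for the primary comparison in steps. The control median in the low-exposure subgroup is 12.6 months. On the effect of the intervention it states: "We expect that TDM-guided dosing can improve PFS in 67% of patients with a low exposure". For those patients, "In this group, a HR (fixed versus TDM-guided dosing) of 2.5 is assumed". In the remaining 33% the HR is taken as one. The section then concludes: "Altogether, this would result in an expected HR (fixed versus TDM-guided) of 2.0".

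The rest of the design follows from that number. "With 67 events, a power of 80% will be obtained to detect this HR of 2 using the log-rank test", at a two-sided 5% level. On the medians: "This translates into an improvement in mPFS from 12.6 months without using TDM-guided dosing to 25.2 months using TDM-guided dosing". With 48 months of uniform accrual, 12 months of further follow-up and no allowance for dropout, this leads to 94 low-exposure patients (47 per arm) and, at 48% low exposure, 196 recruited.

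The Discussion (section 3) returns to the effect size. It calls it slightly challenging and adds: "The HR of 2.0 is a compromise between a realistic but clinically relevant difference and the feasibility of the study". It gives no other derivation.

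**The concern.** The section presents 2.0 as the result of a calculation from stated inputs, and the only simple calculation that returns it is a weighted arithmetic mean of two hazard ratios. That operation is not valid here. Arm B is one population with one hazard. Arm A is the mixture, and its hazard is in the denominator of a fixed-versus-TDM ratio.

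Reversing the ratio shows the problem. For the same patients expressed as TDM versus fixed, the mean is 0.67 x 0.4 + 0.33 x 1 = 0.598, which inverts to 1.67 and not to 2.0. A sound summary cannot depend on which arm is named first.

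The stated power, the event number and the arm A median all rest on the 2.0. If the inputs imply a smaller effect, the chance of missing a real benefit on the primary endpoint is larger than the plan tells its readers and its DSMB.

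**Working it through.** **Inputs (section 2.3.2; allocation ratio from section 2.2).** Control median 12.6 months; HR 2.5 in 67% and HR 1 in 33%; log-rank test, two-sided 5%; 80% power; 47 per arm, 1:1; uniform accrual over 48 months plus 12 months of follow-up; no dropout.

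**Assumptions added.** PFS is exponential, and the 67% and the 33% share one baseline hazard. The plan states neither. The conversion of HR 2 into medians of 12.6 and 25.2 implies the first, and the use of a single control median points to the second.

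**Step 1: reproduce the plan, given HR 2.0.**
- Schoenfeld events: 4(1.96 + 0.842)² / (ln 2)² = 65.3, so 66. The plan's 67 events give power 0.81.
- Probability of an event by month 60: 0.818 in arm B (median 12.6) and 0.601 in arm A (median 25.2). Expected events: 47 x (0.818 + 0.601) = 66.7.
- Recruitment: 94 / 0.48 = 195.8, so 196.
- Simulated log-rank power (20,000 trials, 47 per arm): 0.80.

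Given HR 2.0, the design is sound. The fault is one step earlier.

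**Step 2: where the 2.0 comes from.** 0.67 x 2.5 + 0.33 x 1 = 2.005.

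**Step 3: mix the survival curves in arm A.** With L = ln 2 / 12.6:

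S_A(t) = 0.67 exp(-0.4 L t) + 0.33 exp(-L t)

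- Median: S_A(t) = 0.5 at t = 22.8 months, a ratio of 22.8 / 12.6 = 1.81.
- The HR (fixed versus TDM) is not constant. It is 1.67 at the start, 1.82 at 12 months, 1.96 at 24 months and 2.28 at 60 months, because non-benefiting patients leave the risk set sooner.
- Average (Cox) HR in a very large simulated sample under the planned accrual and follow-up: 1.83.
- Expected events in 94 patients: 67.7.

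**Step 4: power under the mixture.**

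| Scenario (47 per arm) | Events | Power |
|---|---|---|
| Constant HR 2.0, analysis at 60 months | 66.7 | 0.80 |
| 67%/33% mixture, analysis at 60 months | 67.7 | 0.69 |
| 67%/33% mixture, cut at 67 events | 67 | 0.68 |

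Schoenfeld's formula agrees: with 67 events and HR 1.83, (√67 / 2) x ln 1.83 - 1.96 = 0.51, a power of about 0.70.

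**Step 5: sensitivity to the added assumption on prognosis.** The control median is held at 12.6 months and the non-benefiting patients' hazard is varied relative to the others'. Power is about 0.67 to 0.69 at 0.5 to 0.75 times, 0.66 at 1.5 times, 0.62 to 0.63 at 2 times and about 0.56 at 3 times.

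**Step 6: what would give 2.0 or 80%.**
- Benefiting share: 75% gives power 0.78; 77% gives an average HR of 2.01, an arm A median of 25.2 months and power 0.80.
- Events at HR 1.82 to 1.83: about 86 to 88 by Schoenfeld. With the planned follow-up that is about 120 low-exposure patients (60 per arm: 86 events, power 0.80), or 120 / 0.48 = 250 recruited.
- Same 94 patients, 24 months of minimum follow-up: power 0.76.
- Same 94 patients, 36 months of minimum follow-up: about 82 events, power 0.80 to 0.81. Simulated power here exceeds what the formula suggests for 82 events at 1.83, because the HR rises with time.

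**The case against.** Four points can be made for the plan.

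**The Discussion concedes that 2.0 is ambitious.** It does, and a sponsor may choose a target difference on grounds of feasibility. But section 2.3.2 calls 2.0 the expected HR and derives it from 67%/33%; the Discussion never says that this derivation fails. Calling a figure challenging does not correct it.

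**The plan can adapt.** Section 2.5.3 lets the DSMB recommend extending recruitment or follow-up, and the Discussion says that accrual and event rate will be evaluated. Neither would expose this error, because expected events hardly change (67.7 against 66.7). The shortfall is in the size of the effect.

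**The recalculation rests on unstated assumptions.** This stands in part. The 69% should carry its assumptions and not be read as exact. However, the plan attributes part of the 33% to treatment stopped for progression, which suggests a worse prognosis, and that lowers power further. None of the variants tried reaches 80%.

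**The inputs are soft anyway.** The control median has a confidence interval from 9.2 months to not reached, and the 2.5 is observational. True, but that uncertainty is separate from a fixed arithmetic step whose error is known to be optimistic.

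A reader might also infer that extra follow-up simply restores 80%. Section 2.5.1 does not allow that: it caps the study at 6 years, and 48 + 36 = 84 months is 7 years.

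**Conclusion.** The point holds. The HR of 2.0 does not follow from the assumptions given for it. On those assumptions, with exponential PFS and a common baseline hazard, the average HR is about 1.83, the arm A median about 22.8 months and the power about 69%. The type II risk is then about 31%, not 20%. It is higher if the non-benefiting patients have a worse prognosis.

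Three stronger readings are not supported. The counts of 67 events, 94 patients and 196 recruited are not miscalculated; they are consistent once HR 2.0 is taken as given. The starting HR of 1.67, with power of about 56%, is not the right summary either, because the ratio rises over follow-up. And the error does not touch the type I error rate or the planned analysis. It concerns the stated power, expected effect and expected median.

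**What to change.** Amend section 2.3.2 in one of two ways.

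1. **Correct the derivation.** Replace the averaged ratio by the mixture calculation. State an expected average HR of about 1.8, an arm A median of about 23 months, and power of about 69% with 94 patients and about 67 events, naming the assumptions of exponential PFS and equal baseline hazard.
2. **Keep 2.0 as a target detectable difference.** Delete the claim that it follows from 67%/33%, and state that it corresponds to about 77% of low-exposure patients obtaining the full effect.

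Adjust the Discussion's remarks on the HR to match. Either option costs a revised paragraph; the first also means a less favourable stated power.

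Recovering the power is a separate decision for the sponsor. Raising minimum follow-up to 24 months gives about 76% and takes the study to 48 + 24 = 72 months, exactly the 6-year maximum, so it leaves no room for the optional extra year of accrual. Reaching 80% with the same 94 patients needs roughly 36 months and an amended maximum duration. Reaching it with the planned follow-up needs about 120 low-exposure patients, or about 250 recruited.

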#### Duration and termination of the study

2.5.1

It is expected that inclusion of 196 patients will be fulfilled within 4 years. The study is open for enrolment since March 23, 2022 in the first study site. Patients that withdraw from the study within the first 12 weeks may be replaced by other patients. No foreseen risks have been identified that could lead to premature termination of this study. In case of slow accrual, the inclusion period can be extended with one year. With a minimum follow-up of 12 months, the maximum study duration will be 6 years after which analyses will take place.

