#### Data management and study monitoring

2.5.3

Study data will be collected and managed using REDCap electronic data capture tools (23, 24). Eligibility and efficacy parameters, compliance to treatment schedules and parameters necessary to evaluate the study endpoints will be documented in the eCRFs. Data collected in the eCRF are derived from the protocol and collected by the investigators of the study. A clinical research monitor will supervise the data entry and checks whether the study is conducted according to the protocol. Monitoring will take place centrally from the sponsor University Medical Center Groningen and annual monitor visits will take place at the study sites. An independent Data Safety Monitor Board (DSMB), will be installed to monitor all cumulative safety data, accrual, proportion of patients with an alectinib C_min,SS_ < 435 ng/mL and treatment exposure, once a year. The DSMB will recommend the principal investigator to continue the trial as planned, to stop or extend recruitment, to extend follow-up or the DSMB will propose protocol changes.

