In addition, we included exploratory outcomes, a separate consent is needed for each outcome. First, the use of ctDNA measured in plasma is promising in clinical decision-making of patients with NSCLC through its use in predictive testing, detection of resistance mechanisms and monitoring response to therapy (28). In EGFR mutated NSCLC, clearance of ctDNA was found to be predictive of both PFS and OS (28). Nevertheless, prospective data is lacking and there is a need for larger prospective trials collecting ctDNA of specific mutations and TKIs to be able to use this biomarker (28). The ADAPT ALEC trial aims to aid in this demand to prospectively collect ctDNA in patients with ALK+ NSCLC and assess its predictive value of response to alectinib treatment. Considering the long-term survival achieved with alectinib therapy, longitudinal low-grade toxicity becomes more important. Second, a relatively unexplored adverse effect is weight gain, reported in approximately 10% of patients in the pivotal ALEX trial (8). Currently, the etiology and sequelae of alectinib-induced weight gain remain to be elucidated. In this trial, we aim to unravel this phenomenon by prospective analysis of body composition using CT-images made in regular care, in combination with collection of blood samples for measurement of a broad spectrum of satiety and appetite hormones.

Potential limitation of the study design is the relative short follow-up time of 12 months to demonstrate PFS and no marge for ‘non-evaluable’ patients is included in the sample size calculation. The chance that a patient drops out is considered highest in the first 12 weeks after initiation of treatment, when the protocol allows replacement for a new patient. During the study, accrual and event rate will be evaluated. Potential changes in the number of patients to be recruited and/or in duration of follow-up as a consequence of these evaluations will be discussed with the DSMB.

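### The expected HR of 2.0 and the 25.2-month TDM median do not follow from the stated 67%/33% split, which implies an HR of about 1.8 and power below 80%

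*Protocol article*

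**What the plan says.** The protocol article, section 2.3.2 (Sample size calculation), divides the low-exposure patients (C_min below 435 ng/mL) into two groups. For the 67% expected to benefit from TDM: "In this group, a HR (fixed versus TDM-guided dosing) of 2.5 is assumed". For the 33% in whom dose increases are not expected to be feasible, because of toxicity or discontinuation on progression: "so a HR equal to one is assumed for this subgroup". The section then concludes: "Altogether, this would result in an expected HR (fixed versus TDM-guided) of 2.0". No formula is given for combining the two values.

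The rest of the calculation uses 2.0. It gives 67 events for 80% power (log-rank, two-sided 5%), 94 low-exposure patients over 48 months of accrual plus 12 months of follow-up, and 196 recruited. For the medians: "This translates into an improvement in mPFS from 12.6 months without using TDM-guided dosing to 25.2 months using TDM-guided dosing".

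The Discussion (section 3) concedes that 2.0 may be somewhat demanding, calls it a compromise between clinical relevance and feasibility, and ends by calling it achievable.

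**The concern.** A weighted arithmetic mean of hazard ratios depends on which arm is the numerator. Taken as TDM versus fixed, the same averaging gives 0.67 × 0.4 + 0.33 × 1 = 0.598, which is 1/0.598 = 1.67 as fixed versus TDM. One set of assumptions cannot imply both 2.0 and 1.67. A TDM arm in which some patients have a reduced hazard and the rest do not is a mixture of two survival curves, and its HR against the control arm changes over time.

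The primary comparison is sized on 2.0. If the split holds but the implied HR is smaller, the chance of missing the primary result exceeds the stated 20%. The planned checks are unlikely to show this. The Discussion says: "During the study, accrual and event rate will be evaluated", but the expected number of events is nearly the same either way (see the working). The items listed for the DSMB in section 2.5.3 are safety, accrual, the proportion below 435 ng/mL and treatment exposure. The assumed HR is not among them.

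**Working it through.** **Inputs (section 2.3.2).** Control median 12.6 months; HR 2.5 in 67% and 1 in 33%; two-sided 5%; 1:1 allocation, 47 per arm; 48 months of uniform accrual; analysis at 60 months; no dropout.

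**1. The plan's figures, given HR 2.0.**
- Schoenfeld events: 4 × (1.960 + 0.842)² / (ln 2)² = 65.3, so 66. Power at 67 events is 81%.
- With exponential medians of 12.6 and 25.2 months, the event probabilities at 60 months are 0.818 and 0.601. Expected events: 47 × (0.818 + 0.601) = 66.7.
- 94/0.48 = 195.8, so 196.

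Everything after the HR of 2.0 reproduces.

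**2. Where 2.0 could come from.**
- Arithmetic mean of HRs: 0.67 × 2.5 + 0.33 × 1 = 2.005
- Geometric mean: 2.5^0.67 = 1.85
- Averaging the hazards: 1/(0.67/2.5 + 0.33) = 1.67

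Of these, only the arithmetic mean returns 2.0.

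**3. The TDM arm as described.** Let λ = ln 2/12.6 = 0.0550 per month and assume the same control hazard in both subgroups. Then

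S(t) = 0.67·exp(−λt/2.5) + 0.33·exp(−λt).

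- At 25.2 months: 0.67 × 0.574 + 0.33 × 0.25 = 0.467, so the median comes earlier than 25.2 months.
- S(t) = 0.5 at t = 22.8 months.
- HR(t), fixed versus TDM: 1.67 at time 0, 1.82 at 12 months, 1.96 at 24, 2.00 at about 27, 2.09 at 36.
- Event probability at 60 months is 0.622. Expected events: 47 × (0.818 + 0.622) = 67.7, against 66.7 under HR 2.0.
- Average Cox HR over the planned follow-up, from large simulated samples: 1.82 to 1.83.

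**4. Power.**
- Schoenfeld at HR 1.82 and 67 events: ln 1.82 = 0.599; (√67/2) × 0.599 − 1.960 = 0.49, so power is about 69%.
- Events for 80% power at HR 1.82: 4 × (1.960 + 0.842)² / 0.599² ≈ 88.
- Log-rank simulation (20,000 runs per setting, 94 patients):

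| Truth | Power at 60 months | Power at 67 events |
|---|---|---|
| HR 2.0 throughout | 80.6% | 80.1% |
| 67%/33% mixture | 68.9% | 68.0% |

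A separate simulation of the mixture (10,000 runs) gave 68.6% and 67.5%.

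**5. Sensitivity at 60 months (assumed variations).**

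| Variation | Mixture | HR 2.0 |
|---|---|---|
| Weibull shape 0.8 | 65% | 76% |
| Weibull shape 1.2 | 73% | 83% |
| Weibull shape 1.5 | 76% | 85% |
| Control hazard of the 33% at 0.5 times the others' | 67% | not run |
| Control hazard of the 33% at 2 times the others' | 64% | not run |
| Control hazard of the 33% at 3 times the others' | 57% | not run |

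With exponential PFS, a benefit share of 75% gives 78.3% power and 78% gives 81.1%, so about 77% is needed for 80%.

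**The case against.** The best defence is that 2.0 is a target difference. The Discussion describes it as a compromise with feasibility and openly accepts the risk of a negative trial. For that target the events and patient numbers are correct. This stands, and a reader who infers that the sample size arithmetic as a whole is wrong goes too far. It does not rescue section 2.3.2, which presents 2.0 as the result of the split, and the Discussion does not withdraw that.

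Second, the article shows no formula, so the arithmetic mean is an inference from the match at 2.005. That stands too, but the mismatch does not depend on it: the mixture fails to give 2.0 however the figure was reached.

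Third, 69% is not a firm number. It needs exponential PFS, which the plan's own step to 25.2 months and its 94 patients also use. It also needs equal control hazard in the two subgroups, which is doubtful because the 33% includes patients stopping for progression. The split is itself soft. So the documents do not support reading 69% as the trial's actual power; only the direction is stable.

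Finally, a reader might infer that the trial must be enlarged. The documents do not support that either. A sponsor may keep 196 patients and a target of 2.0, provided the text says so.

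**Conclusion.** The point holds as an error of derivation. If the 67%/33% split is right, the plan's own inputs give an average HR of about 1.82 and a TDM median of about 22.8 months, not 2.0 and 25.2. Under exponential PFS and equal control hazard in both subgroups, power with 94 low-exposure patients (67 to 68 events) is about 69%. The risk of a missed effect is then about 31%, not 20%. Across the other assumptions tried, power is roughly 57% to 76%, below 80% in every case. The calculation from HR 2.0 onward is sound.

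**What to change.** In section 2.3.2, do one of two things:

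1. Restate what the split implies: an expected HR of about 1.8, a TDM median of about 22.8 months, and power of about 69% with its range and assumptions.
2. Keep 2.0, label it a target difference in line with the Discussion, and add that it corresponds to a benefit share of about 77%. Stop presenting it as the result of the 67%/33% split.

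Either costs one recalculated paragraph and leaves the design unchanged.

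Optionally, a target of about 88 events can be raised with the DSMB, whose remit includes advising "to stop or extend recruitment, to extend follow-up or the DSMB will propose protocol changes". This is not cheap:

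- Reaching it within 60 months takes about 122 low-exposure patients, or 122/0.48 ≈ 254 recruited. Section 2.3 implies Dutch accrual of 80 × 0.65 × 4 = 208 over four years, so the rest depends on foreign sites whose accrual is not quantified.
- One more accrual year at the planned rate gives 196 × 5/4 = 245 recruited, about 118 with low exposure, and about 82% power at 72 months. Section 2.5.1 ties that year to slow accrual.
- Keeping 94 low-exposure patients and following for 24 months instead of 12 gives about 77%. Following for 36 months gives about 80% but breaks the six-year limit ("the maximum study duration will be 6 years after which analyses will take place").
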